#### Assessment of Eligibility and Randomization

After participants have contacted us by telephone, email or via our social media channels, they will be provided with a link to the online self-report screening (t0, in Unipark; EFS Survey, Questback GmbH, Cologne) through a self-chosen email address. If they fulfill the first inclusion criteria (age, BDDI as is in Table sum score ≥14, and no current psychotherapy), the diagnostician (a clinical psychologist in training) will contact them by email in order to make an appointment to (1) conduct the informed consent procedure and (2) complete the structured clinical interviews. The diagnostician is blind to the condition of the participant both at pre- and post-assessment. In case of crossover (i.e., a participation in ImaginYouth after having participated in SOT before) the ratings will not be blind anymore. The diagnostician will also provide the participants with detailed written information on the study procedure, our privacy policy and a note that it is possible to withdraw from the intervention at any time without facing any consequences. The informed consent procedure and the interviews will be conducted online using RedConnect (RED Medical Systems GmbH, Munich), the latter only after the informed consent form has been sent to the diagnostician by email. If the participants fulfill the remaining inclusion and exclusion criteria, they will then be randomized to one of the two intervention conditions by our external collaboration partners (AM and KS) who, from this point, will not be further involved in the study. A full randomization of the prospective 40 cases will be generated via a list randomizer (RANDOM.ORG, Randomness and Integrity Services Ltd, Dublin) by KS. Once randomization has been conducted, the second first-author (MS; study therapist in both conditions; clinical psychologist in training) will provide participants with a log-in for the intervention to which they have been allocated on the e-mental-health platform Minddistrict (Minddistrict, Berlin).

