### Statistical Methods

All statistical analyses will be conducted using SPSS Statistics (IBM; Armonk, New York, USA) and R (77). Data will be mainly analyzed on an intention-to-treat basis including all randomized participants irrespective of their completion of the intervention. Additionally, study completer analyses including only participants who completed the post-intervention questionnaire battery and interviews will be conducted. Missing data will be imputed. Dropouts and completers will be compared with respect to study variables.

The main analysis focusing on efficacy of ImaginYouth will be analyzed using a repeated measures analysis of variance (rmANOVA) comparing pre- to post- intervention scores of the primary outcome. For the main analysis focusing on superiority of ImaginYouth over the SOT intervention, we will conduct a rmANOVA in the primary outcome between the two intervention conditions and changes from pre- to post-intervention. *Post-hoc t*-tests will be used to examine main effects or interactions in more detail. Cohen's d will be reported as a measure of effect size.

Secondary analyses include the examination of categorical hypotheses [e.g., for the examination of differences between ImaginYouth and SOT in responder (defined as an empirically derived cut-off point of ≥30% reduction from baseline on the BDD-YBOCS), and remission rates (operationalized as a BDD-YBOCS score ≤16 (42))] at post-intervention using Fisher's exact test. Hypotheses on efficacy and superiority regarding self-reported BDD-symptoms severity and associated (comorbid) symptoms will also be tested rmANOVAs (see above). Stability over the follow-up period and differences therein between ImaginYouth and SOT will be tested using a rmANOVA comparing pre-intervention to follow-up scores of self-reported BDD symptom severity. Finally, to examine the feasibility and acceptability of the intervention, the respective measures will be inspected descriptively.

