### Sample Size Calculation

Our a priori power analysis using G^*^Power (78) focused on the main hypothesis of a greater reduction of BDD symptoms in the main outcome measure from pre- to post-intervention in the ImaginYouth than in the SOT group. Thus, we calculated the number of participants necessary to test the interaction effect in a 2 (intervention type) × 2 (repeated measures assessment point) analysis of variance.

The power analysis was based on α= 0.05 and 1-β= 0.95, and an effect size of *f* = 0.36 [yielded by a meta-analysis on effects in internet-based intervention studies in youth by (32)]. The resulting total sample size is *n* = 28. Taking into account expected dropouts [about 30% in internet-based studies; (79)], we aim to recruit 20 patients per study arm type.

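### The primary superiority test amounts to an unadjusted change-score t-test; adjusting for the baseline BDD-YBOCS already collected would use the same data more efficiently

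*Protocol article*

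**What the plan says.** The Statistical Methods section of the Protocol article gives the superiority analysis in one sentence: "we will conduct a rmANOVA in the primary outcome between the two intervention conditions and changes from pre- to post-intervention". The Sample Size Calculation section confirms which term of that model carries the hypothesis, because the sample was sized to "test the interaction effect in a 2 (intervention type) × 2 (repeated measures assessment point) analysis of variance". No baseline covariate is named for this comparison.

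The sizing inputs are given as "The power analysis was based on α= 0.05 and 1-β= 0.95" with an "effect size of *f* = 0.36". The result is reported as "The resulting total sample size is *n* = 28". After an allowance of about 30% for dropout, "we aim to recruit 20 patients per study arm type".

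The Assessment and Data Management section schedules the expert interviews at t1 and t3 only, so the primary outcome has exactly one score before treatment and one after. On allocation, Assessment of Eligibility and Randomization says: "A full randomization of the prospective 40 cases will be generated via a list randomizer".

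**The concern.** With one pre score and one post score per patient, the arm-by-time interaction compares mean change between arms. Subtracting the baseline fixes its coefficient at 1. A regression of the post score on arm and baseline estimates that coefficient instead. When the true slope is below 1, subtracting the whole baseline adds noise that the regression leaves out.

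Precision is at stake. The trial expects about 28 evaluable patients from a population that is hard to recruit, and the baseline score is measured in any case.

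**Working it through.** **Inputs.** From the Sample Size Calculation section: alpha 0.05, power 0.95, f = 0.36, 28 evaluable, 30% dropout, 20 per arm. The article states neither rho nor the SDs, so these are assumptions and ranges are shown.

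**1. Reproducing the plan's figure.** For a 2 × 2 within-between interaction, noncentrality = N·f²·2/(1 − rho), with df (1, N − 2).
- At rho = 0.5 and N = 28: 28 × 0.1296 × 2/0.5 = 14.52, which gives power 0.956. N = 26 gives 0.941, so 28 is the smallest even N.
- Other correlations give other totals: 38 at rho 0.3 and 18 at rho 0.7.
- Dropout: 28/0.70 = 40.

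The stated 28 and 40 therefore reproduce, with an implied rho of 0.5.

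**2. The effect that f = 0.36 implies in that calculation.** For a between-arm difference in change of d baseline SDs, with equal SDs, the change-score noncentrality is (N/4)·d²/[2(1 − rho)]. Setting this equal to 2N·f²/(1 − rho) gives d = 4f = 1.44.

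**3. Same test.** On one simulated data set, the interaction F and the squared change-score t were both 3.339.

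**4. Variances.** Per patient:
- change score: SD_pre² + SD_post² − 2·rho·SD_pre·SD_post
- baseline-adjusted: SD_post²·(1 − rho²)
- difference: (SD_pre − rho·SD_post)², which cannot be negative.

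With equal SDs, the ratio of adjusted to change-score variance is (1 + rho)/2. With unequal SDs it must be worked out from the two expressions, here with SD_pre = 1:

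| rho | SD_post/SD_pre | Adjusted | Change | Ratio |
|---|---|---|---|---|
| 0.3 | 1 | 0.91 | 1.40 | 0.65 |
| 0.5 | 1 | 0.75 | 1.00 | 0.75 |
| 0.7 | 1 | 0.51 | 0.60 | 0.85 |
| 0.5 | 1.25 | 1.172 | 1.3125 | 0.89 |
| 0.5 | 1.5 | 1.6875 | 1.75 | 0.96 |

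**5. Power at rho 0.5 with equal SDs.** The adjusted test has noncentrality (N/4)·d²/(1 − rho²) × (N − 4)/(N − 3), with df (1, N − 3). The last factor is the penalty for chance baseline imbalance. For example, at N = 28 and d = 1.44: 7 × 2.0736/0.75 × 24/25 = 18.58.

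| Difference (SD) | N | Change score | Adjusted |
|---|---|---|---|
| 1.44 (implied by the plan) | 28 | 0.956 | 0.985 |
| 1.0 (assumed) | 28 | 0.72 | 0.82 |
| 0.72 (assumed) | 28 | 0.45 | 0.54 |
| 0.72 (assumed) | 40 | 0.60 | 0.71 |

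Simulation of 20,000 trials per row agreed to within about 0.01 (for example 0.954 and 0.984 in the first row). With no true difference, both tests rejected in about 4.8% of simulated trials at N = 28. At 1.44 SD, the N needed for 95% power falls from 28 to 24.

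**6. Where the gain disappears.** At 0.72 SD, N = 28 and rho 0.5, power moves from 0.36 to 0.38 if the post SD is 1.25 times the baseline SD. At 1.5 times it is about 0.28 for both tests. At rho 0.8 and 1.25 times, rho equals SD_pre/SD_post. Both variances are then 0.5625, and the adjusted test is slightly worse (about 0.67 against 0.69) because only its costs remain.

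**The case against.** The strongest reply is that nothing in the plan is wrong. The hypothesis is a greater reduction, the analysis tests a difference in reduction, and the sample was sized for that same test. The method is standard and holds its type I error. On the plan's own inputs, power is already near its ceiling and the gain is about 3 points. Equal SDs are also doubtful. Entry requires a BDD diagnosis and a screening score of at least 14, which may narrow the baseline spread, while remission in some patients may widen it afterwards. All of this stands, and it limits the point to an efficiency suggestion whose size is conditional.

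Three stronger readings might be inferred, and the article does not support them.

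- **That true power is far below 95%.** The 0.72 SD row comes from reading f = 0.36 as d = 2f. Whether that reading applies depends on the cited meta-analysis, which is not at hand. It is a separate question about the effect-size scale, and the stated N of 28 reproduces as written.
- **That chance imbalance makes the planned test biased.** With 20 per arm, the standard error of the baseline difference is √(2/20) = 0.316 SD, so a gap above 0.3 SD has probability about 0.34. Under randomisation, however, the change-score estimate is unbiased and its standard error already reflects such gaps. Over-correction arises only conditionally on an observed gap.
- **That adjustment makes 40 patients act as about 53.** This ignores the expected dropout. The comparable figure is 28/0.75, or about 37, and only with equal SDs and rho 0.5.

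**Conclusion.** The point holds as an improvement in efficiency. The planned superiority test is valid and unbiased under randomisation, but it does not use the baseline BDD-YBOCS as well as it could.

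The size of the gain rests on rho, the SD ratio and the true difference, and the article states neither rho nor the SDs. With equal SDs and the implied rho of 0.5, the variance falls by a quarter. That is worth about 3 points of power at the planned difference and about 10 points at 0.72 to 1.0 SD with 28 evaluable patients. The gain is small if the post SD clearly exceeds the baseline SD, and nil or marginally negative where rho is close to SD_pre/SD_post.

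**What to change.** In Statistical Methods, define the primary superiority test as a linear model of post-intervention (t3) BDD-YBOCS on arm and baseline (t1) BDD-YBOCS. Report the adjusted mean difference with its 95% CI. Fix this before unblinding. The rmANOVA may stay as a sensitivity analysis.

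Use the same model for the self-report outcomes at t3 and t4, with the pre-randomisation score as covariate. That is t1 where the measure is taken then. For measures that Table 2 schedules at screening and not at t1, such as the Body Dysmorphic Symptoms Inventory and the Dysmorphic Concern Questionnaire, name t0 explicitly.

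In Sample Size Calculation, state the rho that was used and note that the calculation refers to the unadjusted interaction.

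The cost is a few sentences of wording, one degree of freedom and the small imbalance penalty. No new data are needed, and the model runs in the software already named. The downside is little or no gain if rho turns out close to SD_pre/SD_post.

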## Aims of the Study

The main aim of this study is to evaluate the efficacy of an internet-based therapist-guided CBT intervention (ImaginYouth) for reducing symptoms of BDD in adolescents and young adults (in the following named adolescents) and to evaluate its superiority over a supportive online therapy condition (SOT) from pre- to post-intervention. Furthermore, we aim to assess the stability of both efficacy and superiority to follow-up, and the acceptability and feasibility of the intervention format.

We hypothesize that the ImaginYouth intervention will reduce primary expert-rated BDD symptom severity from pre- to post-intervention. Further, we expect the reduction of primary BDD symptom severity to be greater in the ImaginYouth than in the SOT intervention group from pre- to post-intervention. Secondary analyses include the testing of the above-mentioned hypotheses regarding self-reported BDD-symptom severity and associated (comorbid) symptoms. Additionally, we hypothesize that the number of remitted patients and responders will be higher at post-intervention in the ImaginYouth than in the SOT intervention group. Moreover, we expect both the changes and differences between the conditions at post-intervention to be stable over the 4-week follow-up period, and thus hypothesize a significant symptom reduction from pre-intervention to follow-up and a larger symptom reduction from pre-intervention to follow-up in the ImaginYouth compared to the SOT intervention.

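### Fisher's exact test for responder and remission rates is valid but conservative at about 20 per arm; Boschloo's exact test keeps the same 5% level and is never less powerful

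*Protocol article*

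**What the plan says.** The Aims section states a directional hypothesis for both binary endpoints: "we hypothesize that the number of remitted patients and responders will be higher at post-intervention in the ImaginYouth" group than under supportive online therapy (SOT). Statistical Methods lists them as secondary. Response is "defined as an empirically derived cut-off point of ≥30% reduction from baseline on the BDD-YBOCS", remission is a BDD-YBOCS score of 16 or less, and the arms are compared "at post-intervention using Fisher's exact test".

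The main analysis set is intention-to-treat, "including all randomized participants irrespective of their completion of the intervention", with missing data imputed; a completer analysis is added. SPSS and R are the named software.

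Under Sample Size Calculation, "The power analysis was based on α= 0.05 and 1-β= 0.95" refers to the repeated-measures interaction on the continuous primary outcome. After allowing for about 30% dropout, "we aim to recruit 20 patients per study arm type". The article gives no expected responder or remission rates, and no sidedness, separate alpha or power for the Fisher tests.

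**The concern.** Fisher's test conditions on the total number of responders. In a small trial few tables are possible given that total, so the attained error rate usually stays well under the nominal one. The plan then spends less than the 5% it allows itself, and power is lost with no further protection that anyone asked for.

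Boschloo's test is also exact. It takes Fisher's p-value as its statistic and calibrates it over both binomial samples instead of within the fixed margin. At stake is the chance of detecting a real difference in two hypothesised secondary outcomes, in a trial whose size was set for another analysis.

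**Working it through.** **Inputs from the article.** Alpha 0.05, power 0.95, f = 0.36, total 28, dropout about 30%, 20 per arm (Sample Size Calculation); Fisher's exact test (Statistical Methods).

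**Assumptions.** Two-sided 5% for the binary tests; correlation 0.5 between the repeated measures for the sample-size check; all response rates below.

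**1. The plan's own figure.** For the 2 × 2 interaction, λ = f² × N × m / (1 − ρ) with m = 2 and ρ = 0.5, on 1 and N − 2 degrees of freedom. At N = 28, λ = 0.1296 × 28 × 2 / 0.5 = 14.5 and power is 95.6%; N = 26 gives 94.1%. So 28 is reproduced, and 28 / (1 − 0.30) = 40. None of this concerns the binary endpoints.

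**2. Method for the binary tests.** Let a of n₁ (ImaginYouth) and b of n₂ (SOT) be responders.
- Fisher rejects when its two-sided p-value p_F(a,b) ≤ 0.05.
- Boschloo: p_B(a,b) = max over π of Σ Bin(a′; n₁, π) × Bin(b′; n₂, π), summed over all tables (a′,b′) with p_F(a′,b′) ≤ p_F(a,b). Reject when p_B ≤ 0.05.
- Size is the largest rejection probability over a fine grid of common rates π. Power is the sum of binomial probabilities over the rejection region.

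**3. Why Boschloo cannot lose.** The region p_F ≤ 0.05 has size at most 5%. Every table in it therefore has p_B ≤ 0.05, so Boschloo's region contains Fisher's at any arm sizes.

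**4. Exactly 20 vs 20 (21 × 21 = 441 tables).** Fisher rejects in 214 tables, with maximum size 2.53% at a common rate of about 0.34. Boschloo rejects in 234, which are the same 214 plus 20 more, with maximum size 4.64%; in effect it rejects when Fisher's p-value is at most about 0.0915.

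| Assumed rates, ImaginYouth vs SOT | Fisher power | Boschloo power | Gain, points |
|---|---|---|---|
| 60% vs 25% | 49.3% | 58.7% | 9.5 |
| 50% vs 20% | 40.9% | 49.2% | 8.3 |
| 40% vs 10% | 49.2% | 60.9% | 11.7 |
| 60% vs 20% | 65.0% | 72.8% | 7.8 |
| 70% vs 30% | 59.9% | 70.5% | 10.6 |

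(Gains are taken before rounding.) Over a wide grid of rates the gain is 5.9 to 11.7 points where Fisher's power is 20 to 40%, 7.8 to 11.8 at 40 to 60%, 5.4 to 11.0 at 60 to 80%, and at most about 7 above 80%. For example, 70% vs 15% gains 2.7.

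Single tables: 12/20 vs 5/20 gives p = 0.054 (Fisher) and 0.030 (Boschloo); 8/20 vs 2/20 gives 0.065 and 0.039; 10/20 vs 4/20 gives 0.096 and 0.053, so neither rejects.

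**5. Unequal arms (ImaginYouth vs SOT).**

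| Arm sizes | Fisher maximum size | Gain at 60/25 | Gain at 50/20 | Gain at 40/10 |
|---|---|---|---|---|
| 20 vs 20 | 2.5% | 9.5 | 8.3 | 11.7 |
| 19 vs 20 | 3.6% | 4.2 | 2.6 | 0.2 |
| 18 vs 20 | 3.5% | 1.1 | 1.7 | 5.4 |
| 17 vs 18 | 4.1% | 0.6 | 2.6 | 5.5 |

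**6. Completers.** A 30% loss leaves about 28. At 14 vs 14 the maximum sizes are 2.14% (Fisher) and 4.16% (Boschloo), and gains run from 5.2 to 15.7 points over 16 assumed rate pairs (10.4 at 60% vs 25%). At 13 vs 15 the gains for the three pairs above are 9.3, 5.6 and 0.9. What narrows the gap is mostly inequality of the arms, not the smaller sample.

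**7. One-sided 5% at 20 vs 20.** Maximum size 2.66% (Fisher) and 4.28% (Boschloo); gain 5.1 to 11.2 points. The choice of sidedness does not change the picture.

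**The case against.** Fisher's test is a standard, valid choice for a small 2 × 2 table, the endpoints are declared secondary, and no power is claimed for them. All of that stands. Nothing in the plan is incorrect here; the issue is efficiency between two exact tests.

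A reader might infer from the 20 vs 20 figures that the plan's test runs at half its nominal level and throws away 8 to 12 points of power. The documents do not support that as a general statement. Twenty per arm is a recruitment target, equal arms are close to Fisher's worst case, and one patient fewer in one arm lifts its maximum size to 3.6% and cuts the gains in step 5 to between 0.2 and 4.2 points. Even at 20 vs 20 the size of the gain rests on response rates that the article does not state, and some plausible pairs give less than 8.

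A reader might also infer that real findings will be declared non-significant only because of the test. That applies to a few borderline tables such as 12/20 vs 5/20, not to results in general.

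Finally, with dropout expected, a full 20 vs 20 table exists only after imputation. If imputation is multiple there is no single table, and neither the sizes above nor Boschloo's guarantee carries over directly. This stands too, but it applies equally to both tests and gives no reason to prefer Fisher's.

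**Conclusion.** The point holds as an optional improvement of small and conditional size. Two parts need no assumption about response rates: the maximum sizes at given arm sizes (at 20 vs 20, two-sided 5%, 2.5% for Fisher against 4.6% for Boschloo), and the fact that Boschloo's test rejects whenever Fisher's does while keeping the 5% level. The power gain does depend on assumed rates and on the final arm sizes. Near the planned sample it runs from close to zero to about 12 points: about 5 to 12 at exactly 20 vs 20 with moderate power, and often under 6 once one to three patients are missing or the arms differ. All figures are for a single complete 2 × 2 table. The primary analysis is untouched, and Fisher's result, if reported, would be valid.

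**What to change.** Before unblinding, amend Statistical Methods so that the responder and remission comparisons use Boschloo's exact unconditional test at a two-sided 5% level, run in R, in place of Fisher's exact test. How the chosen test is combined over imputed data sets is a separate matter to settle for either test.

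The cost is one sentence, with no extra patients, data or software, since R is already named. The drawback is that Boschloo's test is less familiar to readers and may need a line of explanation in the report.

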### Assessment and Data Management

Detailed self-reports will take place at screening (t0), baseline (t1) prior to randomization, mid-intervention (t2), post-intervention (t3), and 4-week follow-up (t4; see Figure 1 for a detailed overview). On a more regular basis, we will gather brief self-reports on suicidal intent and negative emotions (after each session) as well as on BDD and depressive symptoms (after each module). Self-reported data (t0 through t4) will be collected using the secure online-based assessment system Unipark (EFS Survey, Questback GmbH, Cologne). Expert interviews will be conducted over the internet at t1 and t3 *via* the secure online video conferencing platform RedConnect (RED Medical Systems GmbH, Munich).

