### Outcomes

#### Primary Outcomes

*Yale-Brown Obsessive-Compulsive Scale Modified for Body Dysmorphic Disorder* [BDD-YBOCS; (40); German version: (41)]. The main primary outcome assessing severity of BDD symptoms will be the semi-structured expert clinical interview BDD-YBOCS (40). This will also be used to assess responder and remission status (42). The BDD-YBOCS is the gold standard instrument and assesses both cognitive (e.g., time occupied by thoughts about body defect) and behavioral symptoms (e.g., degree of control over compulsive behavior) of BDD and delusionality using a total of 12 items. The item regarding delusionality will be rated again within the participants' answers on the Brown Assessment of Beliefs Scale [BABS; (43)]. Items on the BDD-YBOCS are rated on a 5-point Likert Scale from 0 to 4, with the scale content depending on the respective item (e.g., 0 = *none* to 4 = *extreme [spends more than 8 h/day on these activities]*). The scale has shown good internal consistency (0.80) and interrater reliability [0.99; (40)].

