**Post−module:**
*after every completed module of the ImaginYouth condition and simultaneously in the Online supportive therapy condition; t0 = self-report screening, t1 diagnostic inteview (baseline), t2 = self-report assessment (mid-intervention), t3 = diagnostic Interview and self-report assessment (post-Intervention), self-report assessment (follow-up)*.

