## Discussion

The aim of this two-arm randomized controlled trial is to evaluate the efficacy of an internet-based therapist-guided CBT intervention (ImaginYouth) and its superiority over SOT for BDD in adolescents. Furthermore, we aim to assess the stability in terms of both efficacy and superiority over a period of 4 weeks post-intervention, as well as the acceptability and feasibility of the intervention format. It is hypothesized that ImaginYouth will reduce primary and secondary BDD symptoms from pre- to mid-, post-, and follow-up assessments. We further expect the reduction of primary and secondary BDD symptoms to be larger in the ImaginYouth group compared to the SOT group from pre- to mid-, post-, and follow-up assessment. Additionally, we hypothesize that the number of remitted patients and repsonders at post-assessment will be higher in the ImaginYouth than in the SOT intervention group.

ImaginYouth provides participants with a CBT-based intervention which makes use of techniques that are currently the first-line treatment recommended in adults (80, 81) and have shown first efficacy in youth as well (82). The ImaginYouth intervention removes some of the treatment barriers which young individuals with BDD might face. Particularly, it might not involve as many feelings of shame. Even though participation is not completely anonymous, contact with study staff (diagnostician and study therapist) do not need to involve personal face-to-face contact. We nevertheless decided in favor of a therapist-guided intervention as guidance has also been shown to increase adherence rates in internet-based interventions (83). ImaginYouth consists of interventions on cognitive, emotional, and behavioral levels, as do treatment manuals for BDD (34, 35). Thus, effects of the intervention should be perceived and measured on all levels (see secondary measures). Moreover, as previous online CBT interventions in BDD have shown (33), effects can also be measured with regard to comorbid psychopathology (e.g., a decrease in depressive symptoms as a consequence of reduced social withdrawal or cognitive restructuring of negative thoughts).

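### The 'stability' test compares pre-intervention with follow-up and leaves out post-intervention, so it shows an effect at follow-up, not a maintained gain; the Discussion also states hypotheses for the primary outcome at times when it is not measured

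*Protocol article*

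**What the plan says.** The Aims section of the protocol article sets out the expectation: "we expect both the changes and differences between the conditions at post-intervention to be stable over the 4-week follow-up period". The same sentence then turns this into a test against baseline, "and thus hypothesize a significant symptom reduction from pre-intervention to follow-up", together with a larger reduction than under SOT. Statistical Methods fixes the analysis accordingly: "Stability over the follow-up period and differences therein between ImaginYouth and SOT will be tested using a rmANOVA comparing pre-intervention to follow-up scores". The closing words of that sentence name the outcome, so the whole comparison is a "rmANOVA comparing pre-intervention to follow-up scores of self-reported BDD symptom severity".

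On the outcome: "The main primary outcome assessing severity of BDD symptoms will be the semi-structured expert clinical interview BDD-YBOCS" (Primary Outcomes). On timing: "Expert interviews will be conducted over the internet at t1 and t3" (Assessment and Data Management). The footnote to Table 2 describes the mid-intervention and follow-up visits as self-report assessments. The Design section says that mid-intervention is not a focus of the main study and is kept for exploratory analyses. The Discussion nevertheless says: "It is hypothesized that ImaginYouth will reduce primary and secondary BDD symptoms from pre- to mid-, post-, and follow-up assessments". Its next sentence makes the matching superiority claim over SOT for the same symptoms and times.

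**The concern.** Stability over the follow-up period is a question about what happens between t3 and t4. The named test uses the pre-intervention score and t4 only. It cannot separate a gain that was kept from a larger gain that was partly lost, because both can leave the same distance from baseline at t4. Stability of efficacy and of superiority is a declared aim of the trial, so a significant pre-to-follow-up result could be reported as maintenance after real relapse.

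A second inconsistency lies beside it. In this article, primary BDD symptoms can hardly mean anything but the expert-rated BDD-YBOCS: the Aims use the word primary for the expert rating, and Table 2 groups the other BDD measures as secondary. Hypotheses for that outcome at mid-intervention and follow-up cannot be tested with the planned interviews.

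**Working it through.** **Inputs from the article (Sample Size Calculation).** Alpha 0.05, power 0.95, f = 0.36 for the interaction in a 2 × 2 design, total n = 28, about 30% dropout, 20 per arm recruited. **Assumed, not in the article:** rho = 0.5 between repeated scores, the size of the within-arm gain, the share lost by t4, and equal SD at each time. The planning effect is carried over to self-report only to give a scale.

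**Step 1: the article's own figure.** With noncentrality λ = N·f²·m/(1 − rho) and m = 2:
- N = 28: λ = 28 × 0.1296 × 2 / 0.5 = 14.52 on 1 and 26 df; power 0.956.
- N = 26: power 0.941.
- 28 / 0.70 = 40.

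So 28 and 40 both reproduce at rho = 0.5 and are not in dispute. In this form f = 0.36 corresponds to a between-arm difference in change of 4f = 1.44 SD. Check: 28 × 1.44² / (8 × 0.5) = 14.52.

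**Step 2: within-arm test, pre versus follow-up.** Noncentral t with noncentrality d·√n / √(2(1 − rho)), which is d·√n at rho = 0.5. Here d is the gain remaining at t4; two-sided 0.05; n = 20 (recruited) or n = 14 (after dropout). With half the gain lost:

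| Gain at t3 | Left at t4 | d·√20 | P(significant), n = 20 | d·√14 | P(significant), n = 14 |
|---|---|---|---|---|---|
| 0.72 SD | 0.36 SD | 1.61 | 0.33 | 1.35 | 0.24 |
| 1.0 SD | 0.50 SD | 2.24 | 0.57 | 1.87 | 0.41 |
| 1.2 SD | 0.60 SD | 2.68 | 0.72 | 2.24 | 0.55 |
| 1.44 SD | 0.72 SD | 3.22 | 0.86 | 2.69 | 0.70 |

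A 0.72 SD gain kept in full also gives 0.86 and 0.70. The test behaves identically for that case and for a 1.44 SD gain half lost, because it sees only the 0.72 SD left at t4.

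**Step 3: between-arm test.** The noncentrality is D·√(N/4) / √(2(1 − rho)), with D the advantage remaining at t4. Starting from 1.44 SD with half lost, D = 0.72:
- N = 40: 0.72 × √10 = 2.28; probability 0.60.
- N = 28: 0.72 × √7 = 1.90; probability 0.45.

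With nothing lost the figures are 0.99 and 0.96. From a 0.72 SD advantage with half lost they are 0.20 and 0.15.

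**Step 4: what a direct t3-to-t4 contrast can do.** At rho = 0.5 the within-arm 95% CI half-width is t(0.975, n − 1)/√n:
- n = 20: 2.093/√20 = 0.47 SD.
- n = 14: 2.160/√14 = 0.58 SD.

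The power to detect a loss of 0.72 SD is 0.86 or 0.70; for a loss of 0.36 SD it is 0.33 or 0.24.

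**Step 5: measurement times against hypotheses.** Expert interviews are at t1 and t3; the Table 2 footnote makes t2 and t4 self-report. The Discussion hypotheses for primary symptoms at mid-intervention and follow-up therefore have no BDD-YBOCS data behind them, and their mid-intervention part conflicts with the Design section. Table 2 lists both self-report BDD severity scales (the Dysmorphic Concern Questionnaire and the Body Dysmorphic Symptoms Inventory) at t3 and t4, so a t3-to-t4 contrast needs no new data.

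**The case against.** Much can be said for the plan. The Aims spell out what is meant by stable, namely a significant reduction from pre-intervention to follow-up and a larger one than under SOT, and Statistical Methods tests exactly that. The pre-to-follow-up group-by-time interaction is a legitimate randomised comparison of the effect at follow-up. Pre-to-post analyses of the self-report measures are also planned, with Cohen's d, so a marked fall in effect could be noticed by setting the two results side by side. All of this stands. What remains is that no t3-to-t4 quantity is named, and the inference labelled stability rests on a test that does not contain t3.

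The probabilities rest on chosen scenarios. The 1.44 SD figure is a between-arm difference; it equals the ImaginYouth gain only if the SOT arm does not change. A reader might infer that the test stays significant after large relapse in general. The lower rows of the table and the between-arm figures do not support that; it can stay significant, depending on the initial gain.

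A reader might also infer that the plan would attach a stability conclusion to the expert-rated outcome, or that the Aims state such hypotheses. Statistical Methods limits the follow-up test to self-report. The Aims never mention mid-intervention, and their follow-up sentence does not name the expert-rated outcome. The conflict is confined to the Discussion, where it drives no planned analysis.

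**Conclusion.** The point holds in two limited parts. First, the test labelled stability omits post-intervention, so significance shows an effect at follow-up and not that the gain was maintained. This follows from the structure of the contrast and needs no numerical assumption. How often it could mislead does depend on assumptions: at rho = 0.5 with half the gain lost, from 0.24 to 0.86 within arm over gains of 0.72 to 1.44 SD, and 0.45 to 0.60 between arms from a 1.44 SD advantage. Second, the Discussion states hypotheses for the primary outcome at two times when it is not assessed, and gives mid-intervention a role that the Design section denies it.

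Both parts concern secondary aims. The primary endpoint, its pre-to-post analysis and the sample size are untouched. The change should be made, but the trial's main inference does not depend on it.

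**What to change.** 1. Keep the pre-to-follow-up rmANOVA on self-report, and label it the effect at follow-up in both Aims and Statistical Methods.
2. Assess stability by the t3-to-t4 change in self-reported BDD severity, in each arm and as a difference between arms, with 95% confidence intervals. Do not conclude stability from the pre-to-follow-up test.
3. In the Discussion, restrict the follow-up hypotheses to self-report, remove the mid-intervention and follow-up hypotheses for the expert-rated outcome, and bring the role of mid-intervention into line with the Design section.

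The cost is wording and one added contrast on scores already scheduled at both times. The real price is that stability becomes harder to claim: with within-arm half-widths of about 0.47 SD (n = 20) or 0.58 SD (n = 14), the trial can exclude only large losses. For that reason a formal margin is not made a condition here; reporting the estimate with its interval is enough. A non-significant t3-to-t4 change should not itself be read as proof of stability.
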